### **13.4.3. Skin function**

The strengths of associations among systemic GC level, skin 11 $\beta$ -HSD1 activity and skin outcome measures will be assessed using Pearson's product moment correlation or, where a bivariate association needs to adjust for a third variable, partial correlation. For severely skewed variables for which a suitable transformation cannot be found, Spearman rank correlation will be used.

### **13.4.4. Feasibility**

Feasibility variables will be summarised descriptively in all patients. They will be interpreted in terms of whether sufficient data were obtained to determine feasibility and if so, whether the data obtained indicate that a larger phase II trial is feasible and what adjustments to protocol, if any, may be needed.

## **13.5. Safety analyses**

See section 13.4.2.2

## **13.6. Definition of 'per protocol' set**

In addition to an intention-to-treat analysis including all patients, a supplemental 'per protocol' analysis (including only those who adhered to the treatment regimen of the programme they were allocated, did not violate the trial protocol in any substantial way, and have data available) will be performed. Prior to unblinding of the study, patients will be allocated to or excluded from the 'per protocol' set by a panel including the clinical project manager, trial statistician, and other appropriate clinical study team members.

## **13.7. Handling of dropouts and missing data**

The level of missing data is one of the feasibility endpoints of this trial. Effective means of imputation such as multiple imputation may prove impractical if the sample size is too small for the imputation model to converge successfully. If multiple imputation cannot be performed, available case analysis will be used, supplemented by last-observation-carried forward single imputation as a sensitivity analysis. Multiple imputation by chained equations will be attempted, using multiple regression as the imputation model. If multiple imputation is viable, both available case and LOCF will be performed as sensitivity analyses.

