## **3. STUDY ENDPOINTS**

### **3.1. Primary endpoint**

24 hour 11 $\beta$ -HSD1 activity in skin (efficacy) at baseline and day 28

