## 9. METHODS OF ASSESSMENT

### 9.1. Assessment of primary variable (AZD4017 efficacy)

#### 11 $\beta$ -HSD1 activity in skin

To evaluate efficacy of oral AZD4017 on 24 hour 11 $\beta$ -HSD1 activity in skin, 3mm punch biopsies will be obtained at Visits 1 and 4 from lower outer forearm (midpoint between wrist and elbow) performed under local anaesthetic (e.g. lidocaine). This procedure will be conducted by authorised trial personnel according to the staff delegation log and does not require sutures. Administration of local anaesthetic may involve a momentary stinging sensation after which the procedure is pain-free. 11 $\beta$ -HSD1 activity assays will be conducted by the Scientific Lead within 8h as previously described [19]. To prevent accidental

unblinding, 11 $\beta$ -HSD1 activity samples will be stored frozen until the blind is broken at the end of the trial and will then be batch processed. Approximately 10% of the sample will be used for validation using a cortisol Enzyme Linked Immunosorbent Assay. Raw data (enrolment number, visit number and date) will be copied in its original form to secure server storage and recorded in the CRF as % conversion of cortisone to cortisol per hour.

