#### 9.2.3.4. Epidermal barrier recovery

In addition to resting TEWL, epidermal function can be assessed by measuring TEWL recovery over time following barrier disruption by repeated tape stripping.

Following the initial TEWL measurement, adhesive patches (D-Squame tapes) will be used to gently remove the *stratum corneum* layers to a pre-specified TEWL rate from the lower inner forearm at Visits 1 and 4. Recovery of TEWL at this location will be evaluated by repeated TEWL readings at 3 hour, 48 hour and 7 days post-disruption at Visits 1, 2, 3, 4, 5 and 6.

This procedure will be conducted by the Scientific Lead and may cause a temporary mild discomfort or transient irritation which should subside within a few hours. The results will be recorded in the CRF and stored as image files in a temporary folder (including enrolment number, visit number and date) on the secure (encrypted) laptop used for the measurements before transfer to a secure server.

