### 13.3. General statistical considerations

Unless otherwise specified, the last valid measurement before study medication administration will be utilized as the baseline value. In general, summary statistics [n (number of available measurements), arithmetic mean, standard deviation, median, minimum, and maximum] for quantitative variables and absolute and relative frequency tables for qualitative data will be presented.

Wherever possible the trial will be reported in accordance with the recommendations of the Consolidated Standards of Reporting Trials statement.

An initial blind review of the data will be completed prior to locking the database to identify patients to be excluded from per-protocol analysis.

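### LOCF in section 13.7 is a weak sensitivity analysis: for the primary outcome it is baseline carried forward, and for the recovery and wound series, read literally, it carries values from the wrong time since injury

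*Protocol*

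**What the plan says.** Section 13.7 of the protocol will attempt multiple imputation by chained equations and warns that the sample may be too small for it. It then fixes two branches.

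- If it fails, available case becomes the main analysis, with "last-observation-carried forward single imputation as a sensitivity analysis".
- If it works: "If multiple imputation is viable, both available case and LOCF will be performed as sensitivity analyses".

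Neither branch is restricted to particular outcomes. Section 13.4.2.1 analyses skin function in the same way as the primary endpoint.

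The measurement schedule decides what LOCF does:

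- **Primary outcome.** Section 3.1 defines enzyme activity "in skin (efficacy) at baseline and day 28". Section 9.1 says "3mm punch biopsies will be obtained at Visits 1 and 4 from lower outer forearm". Under section 13.3, "the last valid measurement before study medication administration will be utilized as the baseline value".
- **Barrier recovery.** Section 9.2.3.4 strips the skin at Visits 1 and 4 and takes "repeated TEWL readings at 3 hour, 48 hour and 7 days post-disruption at Visits 1, 2, 3, 4, 5 and 6".
- **Wound healing.** Section 9.2.3.7 images the wounds at Visits 2, 3, 5 and 6. Section 13.4.1 analyses them at 2 and 7 days for the baseline and the day-28 wounds.

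Section 13.4.1 declares preliminary proof of concept if the adjusted day-28 mean is lower on active than on placebo. Only the sign counts.

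**The concern.** A sensitivity analysis should show whether the conclusion survives a credible departure from the main missing-data assumption. Multiple imputation and available-case analysis both rest on assumptions of the missing-at-random type, so LOCF is the only departure that section 13.7 names. If multiple imputation fails, it is also the only sensitivity analysis.

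For the primary outcome, the only earlier value is the untreated one, so every missing day-28 result becomes no change. That is a single fixed scenario, and its effect on the estimate is known before any data are seen. For barrier recovery and wound healing, the outcome is the state of the skin at a set time after an injury. A value from another time, or from another injury, does not describe that state.

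What is at stake is modest: a disagreement between LOCF and the main analysis could be an artefact of the imputed values, and agreement would reassure little. It still matters somewhat, because section 13.7 makes the level of missing data a feasibility endpoint and section 6.5.2 does not replace randomised participants who withdraw.

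**Working it through.** **The plan's own figures.** Section 13.9 wants 12 completers per arm with 20% drop-out: 12 / (1 − 0.20) = 15 per arm. Section 6.2 gives 30 × 0.8 = 24 completers. Both reproduce. The planned loss is 3 of 15 per arm.

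**Primary outcome: size of the shift.** Let B be mean baseline activity, i the true inhibition and p the share of day-28 values missing on active. Assume placebo does not change and missingness is unrelated to outcome.

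- Active mean under LOCF: (1 − p) × B(1 − i) + p × B = B − (1 − p) × iB
- Placebo mean under LOCF: B
- LOCF difference: −(1 − p) × iB, which is the true difference times (1 − p)

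Section 5.3 reports that healthy-volunteer data suggest about 90% inhibition. Applying that to skin is an assumption. With B = 100:

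- i = 90%: p = 10%, 20%, 30% gives 0.9 × 0.9 = 81%, 0.9 × 0.8 = 72%, 0.9 × 0.7 = 63%.
- p = 20%: i = 80%, 50%, 30% gives 64%, 40%, 24%.
- Unequal loss at i = 90%: 5 of 15 missing on active gives 90 × 10/15 = 60; 1 of 15 gives 90 × 14/15 = 84. The number missing on placebo has no effect here.

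**Primary outcome: why agreement on sign says little.** Set the missing active values to the observed active mean plus a shift δ, and leave placebo alone. The difference is −iB + pδ, which reaches zero at δ = iB/p. LOCF is the single point δ = iB, so it goes only a fraction p of the way to the tipping point, whatever the effect. At p = 20% that is one fifth of the way.

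**Primary outcome: interval width.** Simulation with 15 per arm, 3 missing per arm and 4,000 runs per scenario. Assumed: baseline mean 100, coefficient of variation 30%, baseline to day-28 correlation 0.5. The model adjusts for the baseline value only, a simplification of section 13.4.1.

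| Inhibition | Available case: difference (SE) | LOCF: difference (SE) | Pooled SD, available case → LOCF |
|---|---|---|---|
| 0% | 0.2 (10.7) | 0.1 (8.8) | 29.6 → 29.7 |
| 30% | −29.9 (9.3) | −24.0 (8.5) | 25.6 → 27.9 |
| 50% | −49.8 (8.6) | −39.8 (9.2) | 23.4 → 28.9 |
| 80% | −80.1 (8.1) | −64.1 (11.2) | 21.2 → 32.9 |
| 90% | −89.8 (8.0) | −71.8 (12.1) | 20.7 → 34.9 |

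The standard error falls when the effect is small and rises when it is large, because untreated values mixed into the active arm widen its spread. Correlations of 0.3 and 0.7 show the same pattern. At 30% inhibition or more, the LOCF difference was below zero in at least 99.7% of runs.

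**Barrier recovery and wound healing.** No arithmetic applies. Taking the last available reading literally:

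| Missing reading | Value carried | What it assumes |
|---|---|---|
| 48 h or 7 days, same disruption | 3 h or 48 h reading | No further recovery |
| 7-day wound image, same wounds | 2-day image | No further healing |
| 3 h after the second stripping | 7-day reading after the first | Recovery as far along after 3 hours as after a week |
| 2-day image of the second wounds | 7-day image of the first | A new wound as healed as a week-old one |
| Visit 2 wound image | None exists | Not defined |

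Within an episode the carried value is too early; across episodes it is too late. The two errors point in opposite directions.

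**The case against.** The case on the other side is substantial.

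- **LOCF is secondary.** It is never the main analysis, and available case is also run when multiple imputation works. A reader might infer that it is always the only check; the text of 13.7 does not support that. This stands.
- **No change is an explicit scenario.** It pulls the difference toward zero and is the only planned departure from missing at random, so a result that survives it earns modest reassurance. This stands. A reader might infer that LOCF could overturn proof of concept; under the stated assumptions it cannot reverse the expected sign.
- **The injury series may be carried at matched times.** Section 13.4.1 lists recovery and healing as baseline and day-28 pairs at each time since injury, so LOCF could carry the day-0 3-hour value to the day-28 3-hour slot. Section 13.7 gives no algorithm. The literal result is therefore one reading of an ambiguous rule, and its values are implausible rather than impossible.
- **Detail belongs in the analysis plan.** Variable-level rules usually do, and section 13.10 requires that plan before unblinding. But 13.7 already fixes the method for every outcome without limit, and that choice is the issue.
- **The size is uncertain.** The 90% does not come from skin, where the protocol calls the effect unknown. The 20% is drop-out, not missing biopsies, and section 6.5 lets participants stay for assessments after stopping drug. This stands, so ranges are shown.
- **A tipping point may be uninformative.** With 90% inhibition and 3 of 15 missing, δ = 90/0.2 = 450, so missing active values would have to average 10 + 450 = 460 on a baseline of 100. True, but that shows robustness directly. At 30% inhibition with 5 of 15 missing, δ = 30 × 3 = 90 and the figure is 70 + 90 = 160, which is much closer. LOCF cannot distinguish the two cases.

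**Conclusion.** The point holds as a minor one. For the primary outcome, LOCF is baseline carried forward by design. It shrinks the arm difference by the share missing on active: 90% to 72% at 20% missing, with 81% and 63% at 10% and 30%. This assumes the healthy-volunteer inhibition applies to skin, placebo is unchanged and missingness is unrelated to outcome. It is a weak, single-scenario check of a rule that rests on sign. A reader might infer that single imputation always makes intervals too narrow; under the simulation's assumptions, the standard error moves either way (10.7 to 8.8 with no effect, 8.0 to 12.1 at 90% inhibition).

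For barrier recovery and wound healing, 13.7 leaves open a literal reading that yields clinically implausible values, and nothing in it rules that reading out. The trial is descriptive, and no main result changes.

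**What to change.** Rewrite the LOCF sentences of section 13.7 as follows.

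1. For barrier recovery and wound healing, carry no value across time since disruption or wounding.
2. If LOCF is kept for the primary outcome, call it baseline carried forward and state that it represents no change in those missing.
3. Replace LOCF as the departure from missing at random with a delta-adjusted (tipping-point) analysis around the multiple-imputation estimate or, if that fails, the available-case estimate. Report the shift in missing values that would reverse the sign of the arm difference. In the available-case branch this needs no imputation model: add a shift to the missing values over a grid, refit, and report where the sign changes. Since the criterion is the sign, the interval from that run need not be interpreted.

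The cost is one paragraph of text and a little more analysis work. Data collection and the main analysis stay as they are.

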## **13.8. Planned interim analysis and data monitoring**

In this small study with short follow-up no formal interim efficacy analysis is planned. Data monitoring will be carried out during the trial by the study management team and the sponsor (see section 12.4). . Interim safety monitoring will be conducted by the study Data Management and Ethics Committee. The DMEC independent statistician will obtain the randomisation list from pharmacy and will code this as treatment A or B before passing to the trial statistician. The trial statistician will produce both open (blinded) and closed

(unblinded) reports for the DMEC, the latter using the treatment codes. Only safety data values will be presented by treatment group; data completeness will be summarised for all secondary variables and for biopsy success. Feasibility data will also be presented. The primary outcome will not be available for interim analysis as this will not be calculated until after the final patient completes follow-up. The trial statistician will not be present when closed reports are discussed by the DMEC with knowledge of the codebreak, which will be supplied to committee members by the DMEC independent statistician. The DMEC will examine at least one set of interim safety data after the first 8 patients have completed the trial up to day 35 (or have been withdrawn); timings of subsequent analyses will be informed by the findings of the first analysis.

There will be a blind review of the data after the last patient has completed follow-up.

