#### **6.4.3. Randomization process**

Treatment groups will be allocated on a fully randomised basis. A randomization schedule will be generated by the dedicated trials pharmacy representative who has signed/dated the staff delegation log and is not otherwise associated with this study. Patients will be randomised in a 1:1 treatment allocation ratio to either AZD4017 or placebo. The randomization schedule will be stored in a password protected file accessible only to the dedicated trials pharmacy (the CI and Scientific Lead will be blinded to the randomization process) until all samples have been collected.

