### 8.6. Special warnings and precaution for use

AZD4017 has been studied in healthy human volunteers some patient groups and is generally well tolerated.

The most commonly reported AE amongst healthy volunteers were gastrointestinal disorders and headache and were of mild to moderate intensity. Please refer to IB for more information.

In a multiple ascending dose study (see IB for details) 30 healthy male subjects received single doses of AZD4017 followed by repeated doses of 75 mg once daily up to 900 mg twice daily for 9 days. The expected inhibition on 11 $\beta$ -HSD1 enzyme activity in liver measured by prednisolone generation in plasma after an oral prednisone challenge as well as on urinary GC metabolites was observed. An activation of the HPA axis was also indicated as an increase in both adrenocorticotrophic hormone (ACTH) and dehydroepiandrosterone sulphate levels while cortisol and testosterone levels were unchanged. A few subjects had transient increases in ALT and AST at 1-1.5xULN. One subject taking 1200mg once daily experienced an increase in ALT to 3x ULN. In all cases, liver transaminases returned to baseline on withdrawal of study drug. There is **no clear relationship with plasma exposure as the subjects with the highest ALT did not have the highest plasma area under the curve of either AZD4017** or the glucuronic acid metabolite.

In a Phase IIa trial of subjects with raised intraocular pressure, 7 subjects receiving 200mg AZD4017 once daily and 19 subjects receiving 400mg AZD4017 twice daily for up to 28 days, **no deaths or SAE were reported**; in the group receiving AZD4017 400 mg twice daily three subjects had ALT between 1 and 1.5x ULN, four subjects had AST between 1 and 1.5x ULN, two subjects had gamma-glutamyl transferase between 1 and 1.5x ULN and one subject had GGT between 1.5 and 2x ULN. An activation of the HPA-axis was demonstrated by an increase in ACTH and dehydroepiandrosterone sulfate levels. However, cortisol and testosterone levels were unaffected. No AEs associated with these findings were reported. In the clinical studies performed so far no obvious muscle effects have been seen.

Non-clinical data and observations in previous clinical studies with similar and even higher repeated doses of AZD4017 support dose administration according to the proposed clinical study protocol. Further information regarding non-clinical data and previous clinical studies can be found in the AZD4017 IB.

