#### **13.10. Procedure for unblinding the study prior to analysis**

The final database is not to be locked or unblinded until a review of the data has been completed, the per protocol sample identified, and the statistical analysis plan has been finalised. The dates of each of these milestones will be recorded in the study documentation prior to the full unblinding of the data.

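### The trial statistician holds the A/B-coded allocation list and by-arm safety data during the trial, yet helps set the per-protocol population in a review the protocol calls blind

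*Protocol*

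**What the plan says.** **Release of the list.** Protocol 13.8 names the holder of the key: "The DMEC independent statistician will obtain the randomisation list from pharmacy". It adds that this person, during the trial, "will code this as treatment A or B before passing to the trial statistician". Open and closed reports alike are then written by that recipient; the protocol's own label for the closed ones is "unblinded) reports for the DMEC, the latter using the treatment codes". Their content is limited: "Only safety data values will be presented by treatment group". The first look follows the first 8 patients to reach day 35 or be withdrawn, and the timing of later looks is left open. The trial statistician stays out of the DMEC discussion held with knowledge of the codebreak.

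**Per-protocol set.** Protocol 13.6: before unblinding, "patients will be allocated to or excluded from the 'per protocol' set by a panel including the clinical project manager, trial statistician" and other clinical team members. Sections 13.3 and 13.8 describe this data review as blind.

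**SAP timing.** Protocol 13.10: "The final database is not to be locked or unblinded until a review of the data has been completed", the per-protocol sample is identified and the SAP is final. It does not mention the closed reports.

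**Access to the schedule.** Protocol 6.4.3: "The randomization schedule will be stored in a password protected file accessible only to the dedicated trials pharmacy", until all samples have been collected.

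**Markers in the safety data.** Section 9.2.2.5 lists DHEAS and liver tests among the bloods at baseline, days 7, 28 and 35, and follow-up. On earlier AZD4017 experience, section 8.6 says: "An activation of the HPA-axis was demonstrated by an increase in ACTH and dehydroepiandrosterone sulfate levels".

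**The concern.** Tables by arm cannot be produced without linking each patient to A or B, so from the first look the trial statistician holds patient-level coded allocation. The same person sees safety values split by code, including a marker whose direction under AZD4017 the protocol itself reports. If that marker points to the active code, a member of the per-protocol panel may know or suspect which arm each patient is in.

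Decoding is not strictly necessary. Someone holding the A/B labels can see which coded arm each proposed exclusion falls on, and that already falls short of blind.

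The per-protocol criteria leave room for judgement: 13.4.1 speaks of satisfactory compliance and 13.6 of substantial violations. With 15 randomised and about 12 completing per arm, a single exclusion is a visible fraction of an arm. The final report would describe the set as blindly determined when one of those who set it may not have been blind. Absence from the codebreak discussion does not close the gap, because the list and the by-arm data are already in that person's hands.

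Separately, 6.4.3 and 13.8 cannot both be followed. A look after 8 of 30 patients necessarily comes before all samples are collected.

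**Working it through.** **The plan's own figure.** Section 13.9 needs 12 completers per arm with 20% drop-out: 12 / (1 - 0.20) = 15 per arm, 30 in all. This reproduces, and the point does not depend on it.

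**Can the safety data show which code is active?**

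Inputs from the protocol:
- first look after 8 patients (13.8);
- 1:1 allocation, fully randomised (6.4.3);
- DHEAS measured at visits (9.2.2.5);
- DHEAS increased in earlier AZD4017 studies (5.3 and 8.6).

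Assumptions:
- a true between-arm shift in DHEAS change of d standard deviations, with d = 0.5 or 1 (the documents give the direction, not the size);
- normal data with equal SD in the two arms;
- all 8 patients contribute a value. Withdrawn patients count towards the 8, so fewer may.

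If the reader names the code with the higher mean change as active, then with n per arm

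P(correct) = Φ(d / √(2/n)) = Φ(d √(n/2)).

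For a 4:4 split, √(4/2) = 1.414:
- d = 0.5: Φ(0.707) = 0.760
- d = 1: Φ(1.414) = 0.921

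Section 6.4.3 does not promise a 4:4 split. Under simple 1:1 randomisation of 8 patients, average over the number k in one arm:

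P = Σ [C(8,k)/256] × Φ(d / √(1/k + 1/(8-k))), with 0.5 used for k = 0 or 8.
- d = 0.5: 0.743
- d = 1: 0.902

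The range is therefore about 74% to 92%, against 50% for a guess. At d = 0.25 and 4:4 it falls to Φ(0.354) = 0.638. Only one look is guaranteed, so no figure for later looks is relied on.

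**Liver enzymes.** Section 8.6 reports ALT at 1-1.5x ULN in 3, and AST in 4, of 19 subjects on 400 mg twice daily. It gives no placebo rate. Assuming 0-10% on placebo and 4 per arm, the arm with more cases is the active one with exact binomial probability 0.58 to 0.81 (ties split evenly). This is weaker than DHEAS.

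**Which results could be touched?**
- *Skin 11β-HSD1 activity (primary).* Section 9.1 keeps the samples frozen until the blind is broken and batch-processes them afterwards. Sections 13.6 and 13.10 fix the per-protocol set before unblinding. No values exist when membership is decided.
- *Urinary metabolites, OCT skin thickness and wound diameter.* Sections 9.2.1.1, 9.2.3.6 and 9.2.3.7 place their analysis at the end of the trial.
- *Sudomotor function, hydration, TEWL, barrier recovery and tape counts.* Sections 9.2.3.1 to 9.2.3.5 have these recorded as the visits occur. They are the exposed measures.
- *Intention-to-treat analyses.* Section 13.4.1 includes all patients as randomised, so panel decisions cannot alter them.

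**The case against.** The case against has real weight.

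**The consequence is small by design.** The per-protocol analysis is supplementary (13.4.1), the trial is descriptive with no formal hypothesis tests (13.2), and the proof-of-concept rule rests on the adjusted comparison of skin 11β-HSD1 activity. A reader might infer that the primary result is compromised. The documents do not support that: the primary analysis excludes nobody, and the skin values are generated only after the panel has finished. This part of the objection stands and sets the limits of the point.

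**The masking may hold.** A reader might infer that A/B coding hides nothing in this trial. That cannot be stated as fact. The documents give no size for the DHEAS rise, and the reported rise comes from healthy volunteers and patients with raised intraocular pressure, not type 2 diabetes. At 0.5 SD and 4 per arm, 76% is a hint rather than identification.

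**Code breaks.** A reader might also infer that one emergency code break or unblinded SUSAR would decode all 30 patients. That needs the result to reach the trial statistician, and no section says it would. Section 7.3 says a break will not compromise blinding for other treatments, and 11.6.3 sends unblinded SUSARs from the sponsor to the manufacturer.

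**Existing safeguards and fixed choices.** An independent statistician holds the key, no efficacy values are shown by arm, and a panel rather than one person decides membership. Sections 13.4.1 and 13.7 already fix covariates, interval level, populations and the missing-data approach. The SAP is not at hand and may have been signed early; 13.10 sets only a latest date.

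What survives all this is narrower. The protocol calls a review blind while seating someone who holds the coded list and by-arm data, the per-protocol criteria remain judgemental, and two sections contradict each other on who may hold the schedule.

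**Conclusion.** The point holds in limited form. The A/B coding may not keep the trial statistician blind. For an assumed DHEAS shift of 0.5 to 1 SD, the active code is named correctly about 74-92% of the time at the first look. That range rests on the assumed shift, normality and usable values from all 8 patients. Patient-level A/B labels make the word blind doubtful even without decoding.

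The exposure covers the supplementary per-protocol analyses of measures recorded at visits, and SAP choices still open after the first closed report, notably the per-protocol criteria and the where-necessary transformations. It does not reach the primary intention-to-treat estimate. The conflict between 6.4.3 and 13.8 needs no assumption. The change is worth making because it removes a real gap for little effort, not because the main result is in doubt.

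**What to change.** 1. **13.6:** exclude from the per-protocol panel anyone who has held the coded list or seen a closed report. Another statistician without that access can take the seat.
2. **13.10:** require SAP sign-off, including explicit per-protocol criteria, before the first closed report is produced, and record the date.
3. **6.4.3 and 13.8:** reconcile them by naming who may hold the schedule, and in what form, before all samples are collected.
4. **Optional, 13.8:** the DMEC independent statistician, who already holds the list, runs the closed reports from programs that the trial statistician has prepared and tested on dummy codes. The trial statistician could then stay on the panel.

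Items 1 to 3 cost protocol wording, an earlier SAP deadline and possibly a substitute on the panel. Item 4 adds a little work for the independent statistician at each look. None needs more patients or data.
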